## Methods/design

### Study design

The study design is a single-blind randomized controlled trial that will compare a weight management program with health education. This study will be conducted at the Sport Medicine and Rehabilitation Center, Shanghai University of Sport. A total of 120 prepubescent obese children aged 8 to 10 years old will be included in the study. All participants will be recruited from a local primary school in Yangpu District, Shanghai, China. A multidisciplinary team composed of clinicians, dietitians, and exercise specialists will run the program.

Prior to initiation of the study, all subjects will complete a questionnaire that asks for details, such as medical history. The subjects will also complete the Mini-Mental State examination and Activity of Daily Living test, and describe their exercise habits (frequency and duration). Informed consent will be requested from all subjects and their parents prior to their inclusion in this study.

Participants who meet the inclusion criteria will be allocated in a 1:1 ratio by computer-generated randomization. After randomization, participants will be assigned to either the weight loss group or a health education group (control). This study will include assessments at the following time points: before intervention, after an intervention period of 6 months, and after a further follow-up period of 6 months with no active intervention. The total study period will be 12 months.

### Participants

#### Inclusion criteria

Participants with the following conditions will be included:Obesity according to the childhood obesity definition of the International Obesity Task Force [27];Age: 8 to 10 years;Tanner stage 1 [28];Availability: can participate in three exercise sessions per week for a period of 6 months;At least one parent is willing to attend treatment meetings; andNo family member is currently involved in another weight control program.

#### Exclusion criteria

Participants with any of the following conditions will be excluded:Inability to communicate in Chinese;Diabetes or a psychiatric disorder (for example, schizophrenia, severe autism, mental retardation, or psychosis);Exercise-induced or uncontrolled angina in the past 3 months or severe dyspnea at rest;Medical condition that involves a syndrome cause of obesity or use of medication that influences weight gain or loss;Other illnesses that render participation in this study inadvisable as judged by the participant or study physician.

#### Withdrawal criteria and management

Participants will be allowed or asked to withdraw from the study based on the following:The participant or the participant’s legal representative makes such a request.The participant develops a serious disease, such as heart disease or stroke, and continuing participation becomes unsuitable in the investigator’s opinion.The participant has an adverse reaction related to the weight management program.

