**Methods/design:**

We will conduct a prospective, single-blind, randomized controlled trial with 120 prepubescent obese children. Participants will be randomly assigned to a weight management group or a control group. The weight management group will participate in a dietary and exercise program. The control group will receive health education. After the intervention, participants will be followed for 6 months with no active intervention. The primary and secondary outcomes will be assessed at the baseline, and after 6 months and 12 months. Primary outcome measures will include body weight, body height, body mass index, waist circumference, hip circumference, and body fat percentage. Secondary outcome measures will include three-dimensional functional biomechanics in different tasks, proprioception tests of the knee and ankle, neuromuscular response of the leg muscles, and muscle strength tests of the knee and ankle. Furthermore, adverse events will be recorded and analyzed. An intention-to-treat analysis will be performed if any participants withdraw from the trial.

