**Flow diagram of study design.**

### Statistical analysis

Statistical analysis will be performed using SPSS for Windows version 17.0 (SPSS Inc. Chicago, IL). Data will be presented as the mean and standard deviation in which the distribution of variables is normal. Potential covariates will be determined at the baseline (that is, weight status, growth potential, sex, age, and socioeconomic status), and the difference by study groups or sex will be determined using one- or two-way analysis of variance or *χ*^2^ test. Baseline differences between those who attend and those who do not attend the follow-up measurements will be examined using separate variance *t* tests.

Intention-to-treat analysis will be performed by including all participants in the analysis according to the original group allocation. The follow-up will be maximized regardless of program attendance. A linear mixed model, which includes time (as a repeated factor), group, their interaction, and Bonferroni correction for *post-hoc* multiple comparisons, will be used to determine whether a significant time by group effect exists at the baseline, and after 6 months and 12 months. Average intervention effects of the follow-up period will be estimated and tested using the Bonferroni method for *post-hoc* analysis, in which groups by time interactions are insignificant.

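### The withdrawal rule lets a programme-related adverse reaction end study participation, in practice in one arm only, which conflicts with the stated follow-up policy

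*Protocol article*

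**What the plan says.** The section Withdrawal criteria and management opens with "Participants will be allowed or asked to withdraw from the study based on the following". It then gives three grounds: a request by the child or the legal representative, a serious disease that makes continuing unsuitable in the investigator's opinion, and "The participant has an adverse reaction related to the weight management program". What the child leaves is the study, not the programme. The article describes no step in which a child stops the programme but stays under assessment.

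The Abstract separates the arms by what they receive: "The weight management group will participate in a dietary and exercise program", whereas "The control group will receive health education". The Control group section confirms that controls get lectures and discussion and are asked not to take up other regular exercise programmes.

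The Statistical analysis section states "Intention-to-treat analysis will be performed by including all participants in the analysis according to the original group allocation" and then "The follow-up will be maximized regardless of program attendance". The model is "A linear mixed model, which includes time (as a repeated factor), group, their interaction, and Bonferroni correction" for post-hoc comparisons. Assessments take place at baseline, 6 months and 12 months only (Study design; Outcome measures).

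**The concern.** The third withdrawal ground is defined by the intervention. A control child has no programme to react to, so any loss under this ground falls on the weight management arm. The reason for the loss is how the child tolerated the intervention, which may be related to the outcomes. Gait, stance, muscle strength and proprioception at the knee and ankle are all secondary outcomes that a reaction to exercise could plausibly affect.

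A policy of following children whether or not they attend exists to prevent this kind of loss. If the withdrawal section is applied as written, some children whom that policy is meant to keep may be asked to leave. Two things are at stake: the comparability of the arms at 6 and 12 months, and outcome and safety information on the children who reacted to the programme.

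**Working it through.** **Setting the statements side by side**

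1. Scope: withdrawal is from the study (Withdrawal criteria and management).
2. Trigger: a programme-related adverse reaction is a sufficient ground. Unlike the serious-disease ground, it is not tied to the investigator's opinion that continuing is unsuitable.
3. Exposure: only one arm receives the programme (Abstract; Interventions). The request and serious-disease grounds can apply to both arms, so the asymmetry belongs to this ground and not to withdrawal as a whole.
4. Policy: follow-up is to be as full as possible whatever the attendance (Statistical analysis). A child who stops the programme after a reaction no longer attends it, so this policy says to follow that child. The withdrawal section allows the same child to be asked to leave. The conflict is between these two statements.
5. Data left: the programme lasts 6 months and the first assessment after baseline is at 6 months. A child who leaves the study during the programme therefore has a baseline value only.
6. Model: the stated terms are time, group and their interaction. With only a baseline value, the model in effect assumes that the child's later course resembles that of retained children in the same arm with a similar baseline. No stated term reflects the adverse reaction. The planned comparison of those who do and do not attend follow-up covers baseline differences, so it cannot test that assumption.

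**Illustration of size**

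The article gives no withdrawal rate, effect size or standard deviation, so it has no figure of its own to reproduce, and every rate and effect below is assumed. From the document: 120 children allocated 1:1, so 60 per arm.

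*Scenario A.* A share p of the programme arm withdraws and gets no benefit; the rest gain 0.50 SD. The effect in all allocated children is 0.50 × (1 − p). The effect seen in retained children is 0.50. The bias is 0.50 × p and the relative overstatement is 1/(1 − p) − 1.

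| p | Effect, all allocated | Bias | Overstatement |
|---|---|---|---|
| 0.05 | 0.475 SD | 0.025 SD | 5.3% |
| 0.10 | 0.450 SD | 0.050 SD | 11.1% |
| 0.15 | 0.425 SD | 0.075 SD | 17.6% |

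For scale, the standard error of a simple two-arm difference with 60 per arm is sqrt(1/60 + 1/60) = 0.18 SD.

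*Scenario B.* A share w withdraws, and their outcomes would have been worse than those of retained children by d SD, beyond what the observed data explain. The bias is w × d. With SE = sqrt(1/60 + 1/(60(1 − w))), a true effect of zero and a nominal two-sided 0.05 level, the normal approximation gives the type I error. Power is for an assumed 0.5 SD effect.

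| w | Arms | Bias, d = 0.25 to 1 | Type I error | Power |
|---|---|---|---|---|
| 0 | 60 v 60 | 0 | 0.050 | 78.2% |
| 0.05 | 57 v 60 | 0.01 to 0.05 SD | 0.051 to 0.058 | 77.1% |
| 0.10 | 54 v 60 | 0.03 to 0.10 SD | 0.052 to 0.083 | 76.0% |
| 0.20 | 48 v 60 | 0.05 to 0.20 SD | 0.058 to 0.178 | 73.3% |

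The loss of power is small. Bias is the main issue, and it matters only if withdrawals under this ground are not rare and the withdrawn children differ materially. If d had the opposite sign, the bias would reverse.

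**The case against.** The strongest reply is that the sections can be read together: a child may stop, follow-up is sought anyway, and analysis is by allocation. Several parts of this reply stand.

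- The rule permits or requests withdrawal; it does not impose it. A reader might infer that every child with a reaction is removed, but the text does not say so.
- A reader might infer that intention-to-treat analysis becomes impossible. It does not. A mixed model keeps whatever data a withdrawn child has provided in the allocated group. The analysis is still by allocation, but on a weaker assumption. A commitment to full follow-up is also not a promise that follow-up will be complete.
- A reader might infer that efficacy must be overstated. The documents do not support a direction. An adverse reaction is not the same as a poor outcome, and a child who reacts late in the programme may already have benefited. In Scenario A the bias also vanishes if the programme has no effect.
- A reader might infer that later safety data are certainly lost. The Abstract says adverse events will be recorded and analysed and sets no cut-off at withdrawal. The article may also leave the handling of children after withdrawal to a fuller protocol.
- The Abstract's conditional wording, "An intention-to-treat analysis will be performed if any participants withdraw from the trial", could be read as a second contradiction. It is loose editorial wording. The Statistical analysis section states intention-to-treat without that condition and is the operative text.

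The objection does not remove the conflict in what the article does state. It names the study as what the child leaves, gives a ground that only one arm can meet, and elsewhere promises follow-up that does not depend on attendance. That is a contradiction in the printed text, not an omitted detail.

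**Conclusion.** The concern holds as a conflict between the withdrawal section and the follow-up sentence in the statistical section, confined to one withdrawal ground. Applied as written, that ground allows loss tied to the intervention in the programme arm alone, and the planned model does not reliably repair this for children with baseline data only. The size and direction of any bias cannot be determined from the document. The figures of 0.025-0.075 SD (about 5-18%) rest wholly on the assumed 5-15% withdrawal, no benefit in those children, 0.50 SD in the rest, and no later assessment of anyone withdrawn. If reactions leading to withdrawal are few, the effect on the result is small. The conflict should still be resolved, because doing so is cheap and cannot be done after the children have left.

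**What to change.** Reconcile the two sections by separating stopping the programme from leaving the study, so that a programme-related adverse reaction does not by itself end study follow-up. Unless consent is withdrawn, invite these children to the 6- and 12-month assessments and continue their adverse-event recording. If all of them are assessed, the loss from this source is zero and the arms stay at 60 v 60 as far as this cause is concerned.

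Leave the request and serious-disease grounds unchanged. When or whether a child stops the programme remains a clinical decision and is not addressed here.

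The cost is a change of protocol wording and a line in the consent material. The downside is some extra effort to bring back children who have stopped.

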#### Participant recruitment

Participants will be recruited through advertisements in local newspapers and television, and from primary schools. Study details will be provided to the school administration, school teachers, and parents. Parents will be sent an invitation letter with a tear-off consent slip and a fact sheet. Participants and their parents who show interest in the weight management program will be included in this study.

#### Ethical considerations

This study was approved by the ethics committee of the Shanghai University of Sport (Reference number, 2014–12). Informed consent will be obtained from all participants their parents.

### Interventions

#### Weight management group

A combined dietary and exercise program will be used for childhood obesity treatment, as a systematic review suggests that combined dietary, physical activity, and behavioral components is effective in child and adolescent obesity treatment [20]. Furthermore, a previous study demonstrated the short- and long-term beneficial effects of a combined intervention program among obese children [29].

##### Dietary intervention

The participants and their parents will meet a dietitian six times during the 6 month program. Each family will be instructed to come to the first and last meetings with a completed 12 h dietary recall form [29,30]. The results will be evaluated using computer software and used to educate the participants and their parents on how to eat healthily. The meeting contents will include the reasons and risks of childhood obesity, healthy habits in food choices and food cooking, motivation for weight loss, food pyramid, food labels, eating habits, and recommended food sizes [29,30]. The worksheet and flyers on important nutritional issues will be distributed to the participants and their parents during these meetings. A trained nurse will telephone the parents of the participants in the intervention group once a week to offer support and encouragement [29].

##### Exercise intervention

The exercise intervention program will be adjusted on the basis of a previous study [31]. The participants and their parents will be asked to visit the Sport Medicine and Rehabilitation Center at Shanghai University of Sport once a week during the intervention period. The participants will be instructed to complete a 30 min aerobic exercise session on a treadmill or a bicycle during each exercise session. Each exercise session will be preceded by 10 min of warm-up, followed by 10 min of cool-down and stretching. The exercise intensity will be monitored using a heart rate monitor, and will be equivalent to a raise in heart rate from resting to 65% to 75% of the age-predicted maximal heart rate. An experienced exercise physiologist will be responsible for the training sessions. The participants will be instructed to complete two exercise sessions per week of the same exercise intensity and duration at home. The heart rate will be monitored by a heart rate monitor to ensure that the exercise intensity is consistent for each exercise session. The participants in the control group will be asked to keep their regular exercise habit during the first 6 months.

#### Control group

The participants in the control group will attend a 60 min group session per week. Each session will consist of a 30 min lecture, followed by a 30 min discussion. The lectures will cover health-related topics such as obesity, physical activity, and nutrition. The participants in the control group will be asked to maintain their previous lifestyle and not participate in any other regular exercise programs.

### Outcome measures

All outcome measure assessments will be administered by the main research assistant, who will not be informed of the group allocation, at 2 weeks (baseline), 6 months (follow-up 1, at the end of the intervention), and 12 months (follow-up 2). A demographic questionnaire will be completed at baseline. Demographic information includes the participants’ and their parents’ characteristics (that is, sex, age, ethnicity, family structure, postcode, and socioeconomic status).

#### Primary outcome measures

##### Anthropometric measurements

Body weight and height will be measured with each study participant in minimal clothing and bare feet. Body height will be measured to the nearest 0.5 cm using a fixed stadiometer (Holtain Ltd., Crymych, Dyfed, UK). Body weight will be measured to the nearest 0.1 kg using a standard scale (TBF 543 model; Tanita, Tokyo, Japan). Body mass index will be calculated as:$$ \mathrm{Body}\ \mathrm{m}\mathrm{ass}\ \mathrm{in}\mathrm{dex}=\frac{\mathrm{Body}\ \mathrm{weight}\ \mathrm{in}\ \mathrm{kg}}{{\left(\mathrm{Body}\ \mathrm{height}\ \mathrm{in}\ \mathrm{m}\right)}^2} $$

Waist circumference will be recorded to the nearest 1 mm and measured at the midpoint between the lowest rib and the superior border of the iliac crest using an inelastic measuring tape [32]. Hip circumference will be measured at the maximum posterior extension of the buttocks [32].

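### Height, a listed primary outcome and a component of body mass index, is read only to 0.5 cm while waist is read to 1 mm: a small, avoidable loss of precision, without bias

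*Protocol article*

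**What the plan says.** The abstract of the protocol article names six primary outcomes: "Primary outcome measures will include body weight, body height, body mass index, waist circumference, hip circumference, and body fat percentage". They are measured three times: "The primary and secondary outcomes will be assessed at the baseline, and after 6 months and 12 months".

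The Anthropometric measurements section fixes the reading units. For height: "Body height will be measured to the nearest 0.5 cm using a fixed stadiometer". For waist: "Waist circumference will be recorded to the nearest 1 mm". Weight is read to 0.1 kg. For hip, the section gives the site but no unit: "Hip circumference will be measured at the maximum posterior extension of the buttocks". Height in metres, squared, is the denominator of body mass index. No reason is given for reading height five times more coarsely than waist. The stadiometer's resolution and the number of readings per visit are not stated.

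The Statistical analysis section tests a time-by-group effect in a linear mixed model over the three visits.

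**The concern.** The time-by-group contrast compares the arms on change within child. Rounding error in height must therefore be judged against the spread of change over 6 or 12 months, which is much narrower than the spread of height between children. A unit that looks harmless beside a child's height may not be harmless beside half a year's growth.

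An analysis plan cannot repair this later, because digits that were never written down cannot be recovered. At stake is some precision on one listed primary outcome and, through the formula, a little on another.

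**Working it through.** **Inputs from the documents.** Reading unit for height, 0.5 cm; comparison unit, 0.1 cm (the 1 mm used for waist). Sample size: "A total of 120 prepubescent obese children aged 8 to 10 years old will be included in the study", "allocated in a 1:1 ratio by computer-generated randomization", so 60 per arm. The article states no power, significance level or SD, so there is no figure of its own to reproduce.

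**Assumed inputs.** SD of height change without rounding, varied from 0.3 to 1.5 cm. Two-sided significance level 0.05. True difference set to give 80% power without rounding.

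**Step 1: rounding error.** Rounding to unit u adds variance u²/12 per reading, and 2u²/12 to a difference of two readings.

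- u = 0.5 cm: 0.25/12 = 0.0208 cm² per reading (SD 0.144 cm); 0.0417 cm² per change (SD 0.204 cm).
- u = 0.1 cm: 0.01/12 = 0.00083 cm² per reading (SD 0.029 cm); 0.0017 cm² per change (SD 0.041 cm).

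The finer unit cuts the rounding variance 25-fold.

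**Step 2: effect on height change.** Variance ratio = (SD² + 0.0417)/(SD² + 0.0017). The last column adds, for illustration only, an ordinary measurement error of SD 0.3 cm per reading. This puts 2 × 0.09 = 0.18 cm² into both numerator and denominator.

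| Assumed SD of change (cm) | Variance, 0.1 cm unit | Variance, 0.5 cm unit | Ratio | Power, 0.1 cm unit | Power, 0.5 cm unit | Ratio with added error |
|---|---|---|---|---|---|---|
| 0.3 | 0.0917 | 0.1317 | 1.436 | 79.3% | 63.9% | 1.147 |
| 0.5 | 0.2517 | 0.2917 | 1.159 | 79.7% | 73.7% | 1.093 |
| 0.7 | 0.4917 | 0.5317 | 1.081 | 79.9% | 76.7% | 1.060 |
| 1.0 | 1.0017 | 1.0417 | 1.040 | 79.9% | 78.4% | 1.034 |
| 1.5 | 2.2517 | 2.2917 | 1.018 | 80.0% | 79.3% | 1.016 |

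The power columns leave out the added error. The u²/12 approximation was checked by simulating 1,000,000 children per assumed SD. Relative to unrounded change, the 0.5 cm unit gave variance ratios of 1.464, 1.168, 1.085, 1.044 and 1.016, against 1.463, 1.167, 1.085, 1.042 and 1.019 from the formula.

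The 0.3 cm row shows how steeply the result depends on the assumption, and I do not rely on it. As an observed SD it leaves almost no room for measurement error: an error of 0.3 cm per reading would by itself give a change an SD of √0.18 = 0.42 cm.

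**Step 3: effect on body mass index.** A small height error e moves the index by about 2 × BMI/height × e. At an assumed 25 kg/m² and 1.40 m this is 2 × 25/1.40 = 35.7 kg/m² per metre, or 0.357 per cm. The SD that rounding adds to a change is 0.357 × 0.204 = 0.073 kg/m². Its share of variance is (0.073/0.5)² = 2.1% if the SD of change is 0.5 kg/m², and (0.073/1.0)² = 0.5% if it is 1.0 kg/m².

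**The case against.** The case for leaving this alone has several parts, and most of them stand.

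- **Different units on different instruments are not a contradiction.** Correct. The point is only that one unit is set more coarsely than it may need to be.
- **The size is assumed.** Correct. The documents give no SD, and the result moves from about 16% to about 2% across 0.5 to 1.5 cm. Treating rounding as the only error also overstates the gain: with the illustrative 0.3 cm error the inflation is about 9%, 6% and 3% at 0.5, 0.7 and 1.0 cm. If the spread of growth widens over time, the share is smaller at 12 months than at 6.
- **Height carries no hypothesis.** The stated aim concerns postural stability and neuromuscular control. Even so, the article places height on its primary list and says that the primary outcomes are assessed at every visit.
- **Body mass index is barely affected.** Correct, as step 3 shows.

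Four stronger readings are tempting, and the documents do not support them.

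- A reader might infer bias between the arms. The same rule applies to both, and the assessor is not told the allocation, so the loss is of precision only.
- A reader might treat height as a growth-safety check in a dietary trial of children. No section gives it that role: it appears under anthropometry and in the body mass index formula.
- A reader might convert the largest percentage into a number of children lost from the 120. That presents one assumed SD as established, and it concerns only one outcome.
- A reader might say that the coarse unit saves nothing. That is a reasonable inference, but the stadiometer's resolution and the measuring procedure are not stated.

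**Conclusion.** The point holds as a minor improvement in precision. The article states the 0.5 cm unit, and applies it to a listed primary outcome that also enters another. Compared with 0.1 cm readings, it inflates the variance of height change by about 4% to 16% if the SD of that change is 1.0 to 0.5 cm, and by about 2% at 1.5 cm. Before any measurement error is added, that costs roughly 1.5 to 6 points of power on height in the first range and under 1 point at 1.5 cm. The figures rest on assumed SDs and on rounding errors that are independent between visits, and the inflation shrinks once ordinary measurement error is counted. For body mass index the effect is close to negligible. Nothing here threatens the trial's conclusions.

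**What to change.** In the Anthropometric measurements section, change the reading unit for height from 0.5 cm to 0.1 cm at baseline, 6 months and 12 months, on condition that the stadiometer can be read that finely. State the instrument's resolution there.

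The article gives the trial status as recruitment, so some baseline readings may already have been taken to 0.5 cm. In that case, make the change for all later readings in both arms from the same date and note which unit applied. A change from a 0.5 cm baseline to a 0.1 cm follow-up carries a rounding variance of 0.0208 + 0.0008 = 0.0217 cm², about half of the 0.0417 cm² under the present rule.

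The expected cost is negligible: same instrument, visit and assessor, with one more digit on the form. If the instrument turns out not to show millimetres, the present unit can stand.

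### Raw weight, height and BMI are primary outcomes in growing children, with no age- and sex-standardised index and no covariates in the stated model: interpretation and some precision suffer, but the comparison is not biased

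*Protocol article*

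**What the plan says.** The abstract of the Protocol article (Methods/design) sets the endpoints: "Primary outcome measures will include body weight, body height, body mass index, waist circumference, hip circumference, and body fat percentage". Under Anthropometric measurements, "Body mass index will be calculated as" introduces the usual kg/m² ratio. No z-score, percentile or other reference to age and sex appears among the outcomes. Entry, by contrast, uses a childhood standard: "Obesity according to the childhood obesity definition of the International Obesity Task Force", together with "Tanner stage 1".

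Under Study design, "A total of 120 prepubescent obese children aged 8 to 10 years old will be included in the study", allocation is 1:1 and computer-generated, and visits are "before intervention, after an intervention period of 6 months, and after a further follow-up period of 6 months with no active intervention".

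The Statistical analysis section lists age, sex, socioeconomic status, weight status and growth potential as potential covariates and compares them at baseline by study group or sex. The analysis itself is "A linear mixed model, which includes time (as a repeated factor), group, their interaction", with Bonferroni correction; none of those covariates is placed in it. Baseline counts as one of the three time points. Where the interaction is not significant, an average intervention effect over follow-up is estimated instead, with no stated reference to baseline.

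**The concern.** Children are selected on a childhood definition of obesity and then judged on unreferenced body size over a year of growth. Weight rises as a child grows even when BMI stays constant, so a raw change mixes growth with any change in fatness. Height is itself a primary outcome, although nothing in the stated aim concerns changing it.

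The authors recognised growth, age and sex as relevant, but the model as written does not use them. This matters most in the fallback. If the average effect is taken from the group term, with baseline as one level of time, it compares levels of body size between arms. Such a comparison carries whatever differences the arms happened to have at baseline, and it is noisier than one that uses each child's own starting value.

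**Working it through.** The plan gives no figure on this point to reproduce. From the documents: 120 children at 1:1, so 60 per arm; ages 8 to 10, which can mean a 2-year or a 3-year span; visits at baseline, 6 and 12 months. Every slope, SD, growth rate, effect and correlation below is an assumption.

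**1. Reading a change within one arm.** Weight at constant BMI is BMI × height². At 140 cm and BMI 25:
- growth of 5 cm adds 25 × (1.45² − 1.40²) = 3.56 kg;
- growth of 6 cm adds 25 × (1.46² − 1.40²) = 4.29 kg.

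For BMI, take a programme effect of −0.60 kg/m² at 6 months and a natural rise of 0, 0.8 or 1.2 kg/m² per year. The mean change in the programme arm is −0.60 + 0.5 × rise, which is −0.60, −0.20 or 0.00. The same true effect can look like a clear fall or no change.

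**2. The between-arm contrast.** A simulation used 60 per arm, 4,000 runs, residual SD 2.3, within-child correlation 0.9, ages uniform over 3 years and the same three growth rates. The difference in change between arms was estimated at −0.60 each time, with power 0.89, 0.88 and 0.90. With no true effect (growth 1.2 per year) the rejection rate was 0.05. Common growth cancels.

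**3. Leaving age out of a comparison of levels.** Age SD = span/√12, which is 0.577 years (2-year span) or 0.866 years (3-year span). With weight rising 3 to 5 kg per year of age and a total SD of 8 kg, R² = (slope × age SD / 8)², and adjustment cuts the standard error by 1 − √(1 − R²).
- 2-year span: R² = (3 × 0.577/8)² = 0.047 to (5 × 0.577/8)² = 0.130; cut 2.4% to 6.7%.
- 3-year span: R² = (3 × 0.866/8)² = 0.105 to (5 × 0.866/8)² = 0.293; cut 5.4% to 15.9%.

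For raw BMI (slope 0.5 to 1.2 per year, SD 2 to 3, either span), omitting age inflates the standard error by 0.5% to 17%.

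**4. A chance age imbalance.** The standard error of the difference in mean age is age SD × √(2/60), which is 0.105 or 0.158 years. A 2-SE imbalance shifts raw weight by:
- 2 × 0.105 × 3 to 5 = 0.63 to 1.05 kg (2-year span);
- 2 × 0.158 × 3 to 5 = 0.95 to 1.58 kg (3-year span).

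The unadjusted standard error of a weight difference is 8 × √(2/60) = 1.46 kg, and 2 SE is 2.92 kg. The shift lies inside that allowance.

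**5. What the baseline value adds.** From the same simulation at a BMI rise of 1.2 per year:

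| Analysis of the follow-up visit | SE | Power |
|---|---|---|
| Levels only | 0.461 | 0.25 |
| Change from baseline | 0.187 | 0.90 |
| Adjusted for baseline value | 0.184 | 0.91 |
| Adjusted for baseline value, age and sex | 0.185 | 0.91 |

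As a rough check, baseline adjustment multiplies the standard error by √(1 − 0.9²) = 0.436. At zero growth, 0.414 × 0.436 = 0.180, against 0.183 simulated. The gain would be smaller at a lower correlation. The simulation gives every child the same growth rate and looks at one follow-up visit, so it shows where precision is lost, not the exact amount in this trial.

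**The case against.** The tempting reading is that growth and age mix hide the programme effect, or that a chance age imbalance biases it. The documents do not support this. Allocation is randomised ("Participants who meet the inclusion criteria will be allocated in a 1:1 ratio by computer-generated randomization"), both arms share one visit schedule, and the stated test is time by group, so common growth goes into the time term. Ordinary imbalance is already covered by the unadjusted standard error. The 3.6 to 4.3 kg in step 1 is growth expected in both arms and measures no distortion of the comparison.

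A reader might also infer that no adjustment is intended. That is too strong: the covariates are named, and only their place in the model is open. An article may leave such detail to a fuller plan. This objection has force for the covariates, but the outcome definitions and the listed model terms are stated here.

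The fallback sentence is unclear. If its average is referenced to baseline, most of the precision loss disappears. This stands, and the point about the fallback is conditional on the other reading.

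Finally, raw size is relevant to the hypothesis: the Background and Discussion name body size, body mass and fat distribution as contributors to instability. DXA body fat percentage is also primary and is less directly driven by growth in size, and standardised BMI can compress at high BMI. These are good reasons to keep raw BMI, but not to report it alone.

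**Conclusion.** The point holds as a minor, inexpensive improvement. The primary weight outcomes have no age- and sex-standardised index, and the named covariates do not appear in the stated model. Two consequences follow: within-arm changes in raw weight and BMI cannot be read as weight reduction, and the fallback average, if it compares levels, loses precision and carries baseline differences between arms.

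For raw weight, omitting age from such a comparison costs about 2% to 7% of the standard error over a 2-year age span and 5% to 16% over a 3-year span, given 3 to 5 kg per year of age and an SD of 8 kg. The larger gain comes from the baseline value; once it is included, age and sex add almost nothing under the assumptions used. The time-by-group test is unbiased and already uses each child's baseline, so its validity is not in question.

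**What to change.** For each anthropometric outcome, model the 6- and 12-month values with group, time and their interaction, and with baseline value, age and sex as prespecified covariates, whether or not the arms differ at baseline. Alternatively, keep baseline as an outcome and constrain its mean to be equal in the two arms. Estimate the average follow-up effect from that same model and say that it covers the 6- and 12-month visits.

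Derive age- and sex-standardised BMI at each visit, name the reference in advance (that of the entry definition is the natural candidate), and report it beside raw BMI with a note that it can compress at high BMI. Treat height as descriptive.

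The cost is revised analysis wording and one derived variable. Weight, height, age and sex are already collected, so there are no new measurements. Standardised BMI is less familiar to some readers, which is another reason to show both.
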